## Abstract

**Background:**

Fractures of the odontoid process of the axis are the most common fractures of the geriatric cervical spine. As the population ages, their incidence is expected to increase progressively, as is the number of very old patients (>80 years) with an odontoid fracture. No consensus exists on the optimal treatment (surgical or conservative) and the most relevant outcome parameter (osseous union, fracture stability or clinical outcome). The aim of the INNOVATE (INterNational study on Odontoid frActure Treatment in the Elderly) Trial is to prospectively assess fracture healing and clinical outcome after surgical and conservative treatment for odontoid fractures in the elderly patient, with a specific focus on the very old patient.

**Methods/Design:**

The trial is an observational study in which eleven centres in five European countries are involved. All patients admitted to one of these centres who meet the selection criteria (≥55 years, acute (<two weeks) type II/III odontoid fracture, no rheumatoid arthritis, no ankylosing spondylitis, no previous treatment for odontoid fracture) are asked to participate. The applied treatment is in accordance with usual care and chosen by the treating surgeon and patient. A cohort of 275 patients will be included. Clinical and radiological follow-up moments are scheduled at 6, 12, 26, 52 and 104 weeks, at which both surgeon and patient will complete Case Record Forms (CRFs). The primary outcome will be a combination of fracture healing and clinical outcome at 52 weeks. Osseous union and fracture stability will be assessed with CT-imaging and dynamic X-ray. Clinical outcome will be scored by the Neck Disability Index (NDI) and correlated to the imaging data. Additionally, predefined subgroup analysis will be carried out (i.e. for patient age and osteoporosis) and prognostic factors will be identified.

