### Patient selection

All patients admitted to one of the participating centres who meet the selection criteria will be asked to participate in the study (Table 2). Prior to the start of treatment, the patient will be enrolled by notification to the SIPS Group. The inclusion of patients will continue until the target sample size is reached.

**Table 2 T2:** Selection criteria

**Inclusion criteria**	• At least 55 years old
	• Acute type II and III odontoid fracture based on the classification by Anderson and d’Alonzo (possibly in combination with other fractures); diagnosed using computed tomography
	• Less than two weeks post injury
	• Informed consent
**Exclusion criteria**	• Rheumatoid arthritis
	• Ankylosing spondylitis
	• Previous treatment for odontoid fracture
	• Communication with patient is hampered (e.g. language barrier, severe cognitive impairment, coma)

During baseline and follow-up appointments, radiological and clinical data will be gathered. Patients will also be sent questionnaires to answer at home. Questionnaires will focus on pain intensity, general wellbeing, perceived recovery and illness-related inconveniences.

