### Sample size

Based on the recent literature review, the estimated possible difference in fracture union between the groups is 41% and in fracture stability this difference is 21% [12]. For both union and stability, however, a smaller difference of 20% would be clinically relevant and the study is powered to assess this difference. For the NDI, a 7.5 point difference (on a 50 point scale) is generally accepted as a minimal clinically important difference with a SD of approximately 10 in various psychometric studies [26-29]. Furthermore, it is expected that the number of patients that will be treated surgically will be twice the number of patients that are treated conservatively (2:1) [14]. Since three primary outcome hypotheses will be tested, the significance level (α) has to be divided by three. Based on the primary outcome parameters, the required sample size, assuming α = 0.05/3 = 0.0167 (two-sided) and β = 0.20 (80% power) and an expected drop out rate of 10%, is 275 for union, 198 for stability and 93 for the NDI. In conclusion, 275 patients will need to be recruited in order to give a reliable conclusion to the comparison of union, stability and clinical outcome between the surgically and conservatively treated groups.

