#### Univariate analysis

Univariate analysis will be carried out using χ^2^-tests for dichotomised outcomes and T-tests for continuous outcomes. Intention-to-treat analysis will be used for cases that crossed over to other interventions.

•Primary analysis

The χ^2^-test will be used to test for differences between groups on union and stability at 52 weeks (α = 0.0167). T-test will be used to test for differences between groups on NDI improvement at 52 weeks (α = 0.0167).

•Secondary analysis

The χ^2^-test will be used to analyse the difference in dichotomised NDI. NDI will be dichotomised using the criterium of the minimal clinically important change (improvement) of 7.5 points out of 50. The relation between radiological parameters (union and stability) and NDI will be analysed by comparing the average NDI improvement for patients that acquired union/stability with those that did not.

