#### Multivariate analysis

Multivariate analyses will be carried out using regression models with dichotomised union, stability and NDI as dependent variables, and with the secondary outcome parameters as independent variables and covariates. Propensity score analysis will be used to generate a model to predict the treatment received with the baseline variables:

•Patient age (both dichotomised (≤80 and >80 years) and continuous)

•Fracture characteristics (type of fracture)

•Fracture displacement (in mm and direction)

•Severity of osteoporosis in C2

•Facet joint degeneration in C1-C2

•NDI

•MDI

•VAS neck pain

•SF-36

•EQ-5D

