## Discussion

In this article the rationale and design of a prospective cohort study on surgical versus conservative treatment for odontoid fractures in the elderly is described. There is a lacuna in evidence-based knowledge and guidelines in treating this patient population. To the authors’ knowledge, only one prospective study on this subject has yet been published, involving 159 patients ≥65 years with type II fractures but focusing just on characteristics associated with treatment success or failure and not on describing fracture healing [14]. However, the INNOVATE Trial will specifically aim to evaluate the outcome separately for patients younger and older than 80 years. Moreover, not only fracture union, but also fracture stability will be evaluated in the INNOVATE trial, which will be correlated to clinical outcome. A combination of (relative) fracture stability and favourable clinical outcome might be a legitimate endpoint of treatment in elderly patients, although long term effects have to be investigated. The objective of this trial is to identify which treatment strategy is most favourable for elderly patients with acute type II and III odontoid fractures and to identify factors that predict the success of either one of the available treatment in individual patients. The results of this trial will yield valuable information enabling more rational decision making in the treatment of odontoid fracture in elderly patients.

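### Type II and type III fractures are pooled in a crude primary test, and no treatment effect by fracture type is planned

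*Protocol article*

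**What the plan says.** - **Population.** Table 2 (Patient selection) admits "Acute type II and III odontoid fracture based on the classification by Anderson and d’Alonzo". The Discussion states one objective covering both types: to find the more favourable strategy and the factors that predict success of either treatment in an individual.
- **Treatment choice.** The Background lists fracture pattern first among the grounds for treatment, with the patient's condition and the surgeon's preference. Under Treatment, surgeon and patient decide together; nothing is randomised.
- **Primary analysis.** Under Univariate analysis: "The χ^2^-test will be used to test for differences between groups on union and stability at 52 weeks (α = 0.0167". A t-test does the same for NDI improvement. Neither test is adjusted or stratified.
- **Subgroups.** The abstract says "Additionally, predefined subgroup analysis will be carried out (i.e. for patient age and osteoporosis) and prognostic factors will be identified". The Background mentions predefined subgroups in general and singles out age.
- **Fracture type in the analysis.** It appears once, under Multivariate analysis, as "Fracture characteristics (type of fracture" in the list of baseline variables for the propensity model. The outcome regressions described there take the secondary outcome parameters as independent variables. Those parameters include displacement, osteoporosis and joint degeneration, but not type.

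**The concern.** Two separate things follow if fracture type bears on both the choice of treatment and the chance of healing.

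1. **Confounding.** If type III patients are operated on at a different rate from type II patients, and also heal at a different rate, the crude chi-square compares groups with different type mixes. Part of the observed difference is then due to type and not to strategy.
2. **No effect by type.** Even with type balanced, the plan returns one average over the two types. If the effect differs by type, that average depends on the mix recruited, and no planned analysis would show it. A by-type result added after the data are seen would be post hoc.

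At stake is how far the trial's conclusion can be carried to a patient with a known fracture type.

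**Working it through.** **A. Where type could enter the planned analyses**

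| Planned analysis | Role of fracture type |
|---|---|
| Chi-square on union and stability, t-test on NDI | none |
| Predefined subgroups named | none (age, osteoporosis) |
| Outcome regressions | not among the stated independent variables |
| Propensity model | one predictor of treatment received |

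The propensity model can reduce confounding by type in an adjusted analysis. It does not give an effect by type, and it does not alter the crude primary tests.

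**B. Confounding of the crude test (illustration)**

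Assumptions, none from the documents: type II union 40% conservative v 60% surgical; type III union 70% in both groups; type III share t = 20, 30 or 40%; two thirds of type II operated on.

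Type-balanced effect = (1 − t) × 20 + t × 0, which is 16, 14 and 12 points. If two thirds of type III are also operated on, the crude difference equals this.

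Now let only one third of type III be operated on. At t = 0.3, as shares of the whole cohort:
- Surgical: type II 0.7 × 2/3 = 0.467; type III 0.3 × 1/3 = 0.100. Union = (0.467 × 0.60 + 0.100 × 0.70) / 0.567 = 61.8%.
- Conservative: type II 0.7 × 1/3 = 0.233; type III 0.3 × 2/3 = 0.200. Union = (0.233 × 0.40 + 0.200 × 0.70) / 0.433 = 53.8%.
- Crude difference = about 8 points, against 14 when type is balanced.

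For t = 20, 30 and 40% the crude difference is about 11, 8 and 5 points, against 16, 14 and 12 balanced. The gap of 5 to 7 points is confounding by type. The distance between the balanced figure and the assumed true effects of 20 and 0 is the separate matter of averaging.

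**C. How precise by-type results could be**

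The plan's own figure first. The Sample size section gives 275 for union (20-point difference, alpha 0.0167 two-sided, 80% power, 2:1, 10% dropout) but not the two rates. Rates of 58% v 78% come close, so I use them as an assumption. With mean rate (0.58 + 2 × 0.78)/3 = 0.713:

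n(conservative) = [2.394 × √(1.5 × 0.713 × 0.287) + 0.842 × √(0.58 × 0.42 + 0.78 × 0.22/2)]² / 0.20² = 81.8, so 82.

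Total 3 × 82 = 246, and 246/0.9 = 273.3, so 274 against the stated 275.

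Evaluable patients: 275 × 0.9 = 247.5, about 248. For a type with N evaluable patients split 2:1, the 95% half-width is 1.96 × √[0.58 × 0.42/(N/3) + 0.78 × 0.22/(2N/3)].

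| Group (type III share 30%) | N | Half-width, points | Power for 20 points at alpha 0.0167 |
|---|---|---|---|
| Type III | 74 | 23 | 28% |
| Type II | 173 | 15 | 63% |
| Pooled | 248 | 12 | 80% |

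The half-width for the difference between the two effects (the interaction) is √(22.6² + 14.8²) = about 27 points. If type III is 20% of the cohort, power within type III falls to 19%.

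**The case against.** **The subgroup list may not be closed.** It rests on one i.e. in the abstract; the body gives no full list, and a condensed article may leave that to a fuller document. This has some force. But the article does name its predefined subgroups, and read literally the wording is exhaustive. It leaves out the feature that defines the two-part inclusion criterion, so it needs correcting in the text.

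**Type is already handled as a confounder.** It is in the propensity model, and the Background's fracture pattern is not defined as type II v type III. Both are true. The first does not reach the crude primary tests; the second means that the extent of confounding is unknown, not that it is absent.

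**A reader might infer that surgery works differently in the two types, so that the pooled answer is true for neither.** The documents do not support this. They give no union, stability or NDI rates by type, and a factor that steers treatment is not thereby an effect modifier. The illustration in B also gives conservative union of 54% in the crude case at 30% type III, above the overall 28–44% quoted in the Background. It shows a mechanism, not an expected result.

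**A reader might also infer that the borrowed split undermines the sample size.** The plan says "it is expected that the number of patients that will be treated surgically will be twice the number of patients that are treated conservatively (2:1)" and cites a study that the Discussion describes as "involving 159 patients ≥65 years with type II fractures". But the plan presents the ratio as an expectation and discloses the source and its population. On the assumed 58% v 78%, power is 80% at 2:1, 83% at 1.5:1, 84% at 1:1 and 78% at 1:2. Only a more surgical split costs much (74% at 3:1), and nothing in the documents points to one. I make no point of it.

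**By-type results would be too imprecise to conclude from.** This stands, and it limits the fix.

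**Conclusion.** The point holds as a gap in the planned analysis. The plan enrols two fracture types, says that pattern guides treatment, tests the groups crudely and pooled, and provides no effect by type. The primary tests are therefore open to confounding by type, and the aim of finding factors that predict success of either treatment has no planned analysis for this one.

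The size cannot be taken from the documents. On the assumed rates in B, crude testing understates a type-balanced union difference by 5 to 7 points; other rates or operating patterns would give other values, possibly in the other direction. Any difference in effect between the types is itself an assumption. By-type estimates would be unpowered (about 23 points half-width for union in type III at a 30% share, on 58% v 78%), so they can qualify the Discussion's conclusion but not replace it.

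**What to change.** - In the abstract and under Multivariate analysis, add fracture type (II v III) as a predefined exploratory subgroup.
- Report differences in union, stability and NDI improvement by type, with confidence intervals and a treatment-by-type interaction term.
- Under Univariate analysis, give a type-stratified or type-adjusted overall estimate beside each crude primary test.
- State that the by-type results are unpowered and serve to qualify the overall conclusion.

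**Cost.** A few lines of analysis text. Type is an inclusion criterion diagnosed on CT, so no new data, visits or patients are needed. The price is one more subgroup factor and wide intervals in the smaller type.

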**Discussion:**

Evidence for the optimal treatment for odontoid fractures is lacking. Focusing on both fracture healing and clinical outcome, the results of this study will yield valuable information enabling more rational decision making in the treatment for odontoid fractures in the elderly.

**Trial registration:**

Netherlands Trial Register NTR3630

## Background

In the elderly, odontoid fractures are the most common fractures of the cervical spine [1-6]. As the population ages, their incidence and relevance to clinical practice are expected to increase [7]. The treatment for patients with fractures of the odontoid process is based on the fracture pattern, the patient’s medical condition [2] including age, pain, neurological deficits, and the surgeon’s personal preference. Surgical treatment involves anterior odontoid screw fixation or posterior (cranio)atlanto-axial arthrodesis, leading to prompt stability of the upper cervical spine. However, the condition of the patient may deteriorate by undergoing (major) cervical spine surgery [8]. Especially in the very old (≥80 years of age), a surgical intervention has significant risks for the patient. An alternative to avoid the possible complications of cervical spine surgery is conservative treatment with rigid or non-rigid immobilisation for a longer period of time. However, such immobilisation may eventually result in non-union and prolonged fracture instability, requiring secondary surgery [9]. This unnecessarily lengthens treatment duration and, worse, can cause significant deterioration of the cervical spine anatomy and the patient’s condition [10].

Finding the right balance between fracture healing and treatment complications is difficult. In very old patients, finding this balance is even more challenging. In hospitals where upper cervical spine surgery is frequently performed, it is becoming increasingly common to operate on even the very old patient with a cervical spine fracture. However, debate remains as to whether or not this is indeed a favourable development.

Currently available literature reviews on this topic were inconclusive [11,12]. Recent clinical studies focussed on survival and the occurrence of complications, but not on fracture union and stability [13,14]. All other performed clinical studies were carried out retrospectively, were of limited quality and most did not specifically focus on elderly patients. Moreover, minimal attention was paid to grounds for chosen treatments, and patient groups were often poorly comparable. In the vast majority of published studies, only a small number of patients were included (typically <50).

Furthermore, the goal of treatment is still debatable. It is unknown whether or not non-union always leads to complaints in the patient. Consequently, debate remains as to whether the goal of treatment should be osseous union, fracture stability or a favourable clinical outcome. The measurement of these parameters is likewise not uniformly described. The available literature shows higher osseous union rates in surgically compared to conservatively treated patients (66–85% and 28–44%, respectively), but patient selection mechanisms may have profoundly interfered with these outcome percentages. The majority of patients achieved fracture stability regardless of the applied treatment (82-97% in surgically treated patients and 53-79% in conservatively treated patients). There are insufficient data available, especially from direct comparisons, to determine the difference in clinical outcome between surgical and conservative treatment strategies. There is no evidence that clinical outcome correlates better to fracture union than to fracture stability, or that the quality of union, whether it be osseous of fibrous, influences clinical outcome [12].

The goal of this study is to prospectively compare fracture union, fracture stability and NDI improvement at 52 weeks between surgical and conservative treatments in patients over 55 years of age with acute type II and III odontoid fractures. Predefined subgroup analysis may offer prognostic factors that can predict the success of either a surgical or conservative treatment. The influence of age (≥55-80 and ≥80 years) on treatment outcome will particularly be studied. The outcome of this study will yield valuable information enabling more rational decision making in treating the elderly patient population.

## Design and methods

The INNOVATE (INterNational study on Odontoid frActure Treatment in the Elderly) Trial is a prospective, comparative cohort study with two parallel groups. A multi-centre study is necessary to include the required number of patients in a favourable time frame and to obtain generalisable results. The trial will be conducted in eleven hospitals in five European countries (Table 1). Medical ethical approval was obtained in all participating centres prior to the start of the study. In a number of other hospitals, the trial is still pending approval after which these centres will also participate. The participating centres are individually responsible for the treatment applied. The coordination of the study will be carried out by the Spine Intervention Prognostic Study (SIPS) Group of the Leiden University Medical Centre. Experienced in conducting multi-centre national and international studies, the SIPS Group has established research databases and has a group of research nurses available. The research nurses will monitor data collection and can be consulted by surgeons and patients who have questions about the study protocol or the treatment of individual subjects. The main research question will be answered at 52 weeks of follow-up. The complete follow-up period will be 104 weeks (Figure 1).

### Patient selection

All patients admitted to one of the participating centres who meet the selection criteria will be asked to participate in the study (Table 2). Prior to the start of treatment, the patient will be enrolled by notification to the SIPS Group. The inclusion of patients will continue until the target sample size is reached.

**Table 2 T2:** Selection criteria

**Inclusion criteria**	• At least 55 years old
	• Acute type II and III odontoid fracture based on the classification by Anderson and d’Alonzo (possibly in combination with other fractures); diagnosed using computed tomography
	• Less than two weeks post injury
	• Informed consent
**Exclusion criteria**	• Rheumatoid arthritis
	• Ankylosing spondylitis
	• Previous treatment for odontoid fracture
	• Communication with patient is hampered (e.g. language barrier, severe cognitive impairment, coma)

During baseline and follow-up appointments, radiological and clinical data will be gathered. Patients will also be sent questionnaires to answer at home. Questionnaires will focus on pain intensity, general wellbeing, perceived recovery and illness-related inconveniences.

### Treatment

The treating surgeon and patient will make a shared decision as to whether surgical or conservative treatment will be applied. Participating centres and surgeons are all able to facilitate and respectively carry out both surgical and conservative treatments.

#### Surgical treatment

Surgical treatment can be carried out by either an anterior or posterior approach. In an anterior approach, a single or double odontoid screw is inserted through the corpus of C2 into the odontoid process to directly stabilise the fracture (anterior odontoid screw fixation). In the posterior approach, fixation of the C1-C2 vertebrae is carried out, thereby indirectly immobilising the odontoid process as well (C1-C2 arthrodesis). The posterior technique is sometimes extended cranially to C0 or caudally to C3 or lower, possibly leading to increased stability but further limiting the cervical range of motion. A CRF will register the procedures/findings of the surgeon and the motivation for the chosen surgical treatment strategy.

